**PATHWAY study: Statistical Analysis Plan for WS3+ RCT outcomes at 4 months**

**Version 2 with amendment to the MCQ-30 secondary outcome specification 24/03/2021**

1. **Introduction**

This document presents the SAP for WS3+, an extension of the WS3 study. The original Pathway WS3 was designed as a feasibility study of home-based MCT. The study included quantitative and qualitative work to assess the feasibility of conducting an RCT of Home-MCT, including acceptability to patients and the processes of recruitment, randomisation, treatment, and data collection at baseline and follow-up; together with a pilot study designed as a miniature version of a full RCT to test whether all the components of the main study would work together smoothly. Additionally, to collect data on patient variables and outcome measures to inform the design and sample size for a full-scale trial and establish provisional evidence of the effectiveness of Home-MCT at reducing anxiety and depression symptoms.

In January 2019 analysis of recruitment and qualitative data collected under the study concluded that provision of Home-MCT had proved acceptable to patients, recruitment had been to target and on time, and that a high 4-month retention rate had been achieved. Analysis of the pilot baseline outcome data indicated that rates of missing data were low and the outcome measures demonstrated sufficient variability to detect change. With a view to potential extension of the data collection (see below), we used the following strategy: 1) all analysis was conducted without breaking the blinding of the PI or trial statisticians; 2) no separate trial-arm analysis was undertaken, and 3) none of the 4- or 12-month outcome data was examined, except for 4-month completion rates. Consequently, no estimate of the effectiveness of Home-MCT was made from the data collected under the pilot since our aim was to extend data collection and use the pilot as an internal-pilot study.

On the basis of these results and after full discussion with the trial steering committee (TSC), a variation to contract (VTC) application was made to the NIHR to utilise a project underspend to extend the study into a definitive trial of the intervention, called WS3+, through the recruitment of additional patients. No changes were required to the method of recruitment into the trial and the randomisation procedure did not change. Also, all outcome measures remained the same, including total score on the HADS as the primary outcome. In view of there being no substantial changes to any of the trial processes or instruments and that the pilot data had not been unmasked or any arm-based analysis conducted, the VTC proposed that the pilot trial sample and the additional participants be combined into a single sample for the purposes of analysis of the WS3+ RCT.

NIHR approval for the variation to contract was obtained on 12/03/2019. Recruitment to WS3+ commenced on 27/05/2019, representing a 65 week break since recruitment of the last participant to WS3. Two differences from WS3 should be noted: (1) in order to achieve the target sample, recruitment was extended to include two additional hospital Trusts; (2) to complete WS3+ within the timeline of the Pathway programme, follow-up data collection was restricted to 4 months HADS (the primary outcome) and no 12-month follow-ups were conducted.

**Sample size**

The WS3 pilot trial had a planned total sample size of 108, using 1:1 random assignment to Home-MCT plus usual CR or usual CR alone. Participant allocation was undertaken by a blinded statistician using a sequence based on randomised blocks of size 6 and 4, stratified by site, gender and whether they suffered from anxiety, depression or both.

WS3+ utilised an identical randomisation procedure and was powered to detect an effect size of 0.4 on total HADS score at 90% power, assuming a 0.5 correlation between HADS at baseline and FU 20% drop-out at 4 months follow-up (based on WS2). This indicated a total recruitment target (i.e. including the internal pilot participants) of 123 per arm, aiming to collect 4month FU on 98 of these in each arm.

In March 2020 the UK was put into lockdown as a result of the covid-19 pandemic. Covid interfered with participation in CR and also with the entry of CR attendance data into the database. Since it was unknown how long the lockdown would be in place, a decision was taken to review the data collected to date, to determine if it was feasible to halt any further data collection. The table below shows the target and achieved samples at baseline and 4 months as of 06/04/2020

WS3+ (Total Target: 246):

|  | MCT + CR | | | CR | | |
| --- | --- | --- | --- | --- | --- | --- |
|  | Target sample | Achieved sample | Number known to have completed CR | Target sample | Achieved sample | Number known to have completed CR |
| Baseline | 123 | 119 | - | 123 | 121 | - |
| 4 months FU | 98 | 76 (84)* | 58 | 98 | 100 (105)* | 61 |
| *including patients who returned the primary outcome (HADS) only | | | | | | |

On the basis of the samples for which the primary outcome at 4-months was available (MCT+CR=84; CR=105), the available power to detect the target effect of 0.4 was computed to be 88%. For the secondary outcomes (MCT+CR=76; CR=100) the power to detect an effect of 0.4 was 86%.

On the basis of the above, in discussion with the TSC it was decided that recruiting additional participants into WS3+ would have quite limited benefit, and that study resources would be better deployed at aiming to collect the outstanding 4 month FUs from current participants. This should also aim to reduce the imbalance between trial arms in the numbers with outstanding 4-month FUs to collect.

1. **Main analyses of Primary Outcomes**

*Research Null hypothesis:*

There is no significant difference in the primary outcome between usual cardiac rehabilitation (CR) and home-based (self-help) metacognitive therapy (MCT) plus usual cardiac rehabilitation at 4 months. The primary endpoint will be the following outcome measured at 4 months:

| **Primary outcome** | **Description** |
| --- | --- |
| Hospital Anxiety and Depression Scale (Total score) | A 14-item measure of anxiety and depression designed for use in non-psychiatric hospital clinics. |

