**Planned statistical methods**

Test of the intervention: The effect of the intervention will be examined using the treatment group by time-point interaction term from a multi-level, mixed effects, regression model analysis combining both time-points (baseline and 4 months). The primary endpoint is HADS total score at 4 months, for which the interaction component relating to 4 months (relative to baseline) will be used.

The primary analysis will take the form of an intention-to-treat analysis using complete cases. This will be supplemented by a sensitivity analysis using multiple imputation, allowing us to assess the robustness of the results against missing values (see below). Other sensitivity analyses will be conducted as appropriate (see below). Analysis will be conducted using Stata 15 and an alpha level of 5%.

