**Analysis method**

The primary outcome is assumed to be a continuous longitudinal variable for which linear regression is appropriate. The model will have two levels: time-points within patients**.** Random effects will be applied to the patient-specific intercepts.

1. Outcome: HADS total score at baseline and 4 months.
2. Fixed effects: trial arm, time-point, arm x time-point, design variables (hospital site, sex), other pre-specified covariates and additional covariates (see Choice of Covariates, below).
3. Random effects: patient.

Time-point will be treated as a discrete variable.

In terms of the covariance matrix chosen for the mixed effects model, both an unstructured and a first order autoregressive covariance matrix will be explored. The one with the lowest Bayesian information criteria will be selected.

Alternative tests if violation of distributional assumptions

See distributional tests below.

Sensitivity analysis

See relevant section below

1. **Analyses of Secondary Outcomes**

Research hypotheses:

There are no significant differences in the secondary outcomes between usual cardiac rehabilitation (CR) and home-based (self-help) metacognitive therapy (MCT) plus usual cardiac rehabilitation at 4 months. For the secondary outcomes, tests of an intervention effect will be assessed using the mixed-effects model interaction between treatment arm and time-point.

| **Secondary outcome** | **Description** |
| --- | --- |
| HADS anxiety score | Score based on summing across the 7 anxiety-specific items from the HADS |
| HADS Depression score | Score based on summing across the 7 depression-specific items from the HADS |

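### The stated power (90%, later 88% and 86%) is that of a baseline-adjusted analysis; the planned arm by time-point test has about 80%, 78% and 75%

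*SAP*

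**What the plan says.** Under Sample size, the SAP states that WS3+ was "powered to detect an effect size of 0.4 on total HADS score at 90% power, assuming a 0.5 correlation between HADS at baseline" and follow-up, with "20% drop-out at 4 months follow-up (based on WS2"). This gives 123 recruited and 98 followed per arm. On the counts of 6 April 2020 it adds, for the primary outcome with 84 and 105 patients, that "the available power to detect the target effect of 0.4 was computed to be 88" per cent. For the secondary outcomes with 76 and 100 patients, it says "the power to detect an effect of 0.4 was 86" per cent. It names no test or formula behind these figures.

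The test is fixed under Planned statistical methods for the primary outcome: "the treatment group by time-point interaction term from a multi-level, mixed effects, regression model analysis combining both time-points (baseline and 4 months"), on complete cases, at a 5% alpha. Under Analysis method, the HADS total at both time-points is the outcome, with a random patient intercept and "Fixed effects: trial arm, time-point, arm x time-point" plus covariates. Baseline score is not among the covariates in Tables 1 and 2. The secondary outcomes use the same model.

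**The concern.** A baseline to follow-up correlation enters a sample size calculation because the analysis is expected to gain precision from baseline. How much it gains depends on the analysis. ANCOVA removes a share r² of the variance. A comparison of change scores replaces the variance σ² by 2(1 − r)σ², which at r = 0.5 is σ² again, so nothing is gained. The planned model includes an arm main effect, so it estimates a separate baseline mean in each arm, and its interaction term is a change comparison.

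If the power was computed for ANCOVA, the primary test is weaker than the plan claims, and so is the test of every secondary outcome. A null result would be read against an 88% that the test does not have. The 2020 judgement that further recruitment would add little also cited these power figures.

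**Working it through.** **Inputs (SAP, Sample size and Planned statistical methods).** Effect d = 0.4 SD; r = 0.5; target power 90%; drop-out 20%; alpha 5%; numbers with follow-up 98/98 (target), 84/105 (primary) and 76/100 (secondary). Two assumptions are added. The test is two-sided, which the SAP does not say, and the SD is the same at baseline and 4 months, which is the usual reading of one effect size with one correlation.

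**Step 1: reproduce the plan's figures.** With variance factor f,

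n per arm = 2(1.960 + 1.2816)² × f / d²

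power = Φ( d / √[f(1/n₁ + 1/n₂)] − 1.960 )

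ANCOVA has f = 1 − r² = 0.75. Then n = 2 × 10.508 × 0.75 / 0.16 = 98.5, and 98.5 / 0.8 = 123.1. These match 98 and 123. The powers are in the table and match 90%, 88% and 86%.

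**Step 2: the planned test.** With complete pairs and a free mean for each arm at each time-point, the interaction estimate is the difference between arms in mean change. Its factor is f = 2(1 − r) = 1.0.

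| Followed | 1/n₁ + 1/n₂ | SE, f = 0.75 | Power, ANCOVA | SE, f = 1.0 | Power, interaction | SAP states |
|---|---|---|---|---|---|---|
| 98/98 | 0.02041 | 0.1237 | 89.9% | 0.1429 | 80.0% | 90% |
| 84/105 | 0.02143 | 0.1268 | 88.4% | 0.1464 | 78.0% | 88% |
| 76/100 | 0.02316 | 0.1318 | 85.9% | 0.1522 | 74.8% | 86% |

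For 90% power the interaction test needs n = 2 × 10.508 / 0.16 = 131.3, so 132 followed and 132 / 0.8 = 165 recruited per arm. At 90% power it detects (1.960 + 1.2816) × SE: 0.46 at 98/98, 0.47 at 84/105 and 0.49 at 76/100. The ANCOVA values are 0.40, 0.41 and 0.43.

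**Step 3: could another reading give the stated figures?** A one-sided change comparison needs 108 per arm and has 87.6%, 86.2% and 83.7% power, so it does not reproduce 98 per arm, 90% or 86%. Using the t distribution alters each power by about half a point or less (ANCOVA 89.6/88.1/85.5%; change 79.6/77.6/74.3%).

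**Step 4: is the interaction really the change score?** In three simulated complete-pair data sets of 84/105, a random-intercept model with a time-constant covariate gave the same estimate and SE as a change-score regression. In the first, both gave −0.5736 with SE 0.1319; ANCOVA on the same data had SE 0.1175. Covariates that do not vary with time cancel from the contrast, and with two time-points and complete pairs the choice of covariance matrix does not alter the estimate.

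**Step 5: keep the baselines of patients without follow-up.** The variance becomes (1 − r²)(1/n₁ + 1/n₂) + (1 − r)²(1/N₁ + 1/N₂), where N is the number with baseline. At 84/105 with N = 119 and 121 this is 0.75 × 0.02143 + 0.25 × 0.01667 = 0.02024, SE 0.1423, power 80.3%. The other two are 82.0% (98/98, N = 123 each) and 77.8% (76/100).

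**Step 6: sensitivity to r.** The interaction test has 72.4/70.3/67.0% at r = 0.4 and 87.9/86.3/83.6% at r = 0.6. ANCOVA is higher at both (86.3/84.6/81.8% and 93.8/92.7/90.8%).

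**The case against.** The size of the gap depends on equal SDs, which the SAP does not give. Let k be the ratio of baseline to follow-up SD, with the effect in follow-up SD units. The factor is then 1 + k² − 2rk, and at r = 0.5 and 84/105 the power is 88.4% for k = 0.5, 84.6% for 0.8, 81.7% for 0.9, 78.0% for 1 and 73.7% for 1.1. A sample selected on symptoms could have a narrower baseline spread. This stands as a condition on the size of the loss. It does not rescue the stated figures: the gap closes only at k = 0.5, and the interaction does not beat ANCOVA at any k.

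The formula behind the SAP's power is inferred. That is true, but one factor reproduces the sample size and all three powers.

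Complete cases might mean only that nothing is imputed, with baseline-only patients kept. The powers are then 82/80/78%, still about 8 points short.

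The effect on the 2020 decision should not be pressed. By then 119 + 121 = 240 of 246 had been recruited, and moving from 98/98 to 84/105 costs 2.0 points under the interaction and 1.5 under ANCOVA. Stopping just short of target was reasonable under either test. What the error undermines is the reassurance drawn from the level of power, and the original target. The 84/105 and 76/100 are also interim counts, with further follow-up to be collected.

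Finally, the interaction test is valid: unbiased under randomisation, with its type I error controlled. The fault is lost efficiency and an overstated power, not bias.

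**Conclusion.** The concern holds. The sample size section and the analysis section describe two different tests. On the SAP's own effect size and correlation, with a two-sided 5% test and equal SDs, the planned primary test has 80.0% power at the design numbers and 78.0% at 84/105, against 90% and 88% stated. The secondary tests have 74.8% against 86%. At 84/105 the risk of missing a true effect of 0.4 is about 22% rather than 12%. Keeping baseline-only patients narrows the shortfall by 2 to 3 points. A correlation above 0.5 or a smaller baseline SD would narrow it too; a lower correlation or a larger baseline SD would widen it. This should be corrected before the analysis, because it affects the primary test and the lost power can be recovered without another patient.

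**What to change.** Make the primary analysis, and each secondary analysis, a regression of the 4-month score on arm with the baseline value of the same measure as covariate, alongside the covariates already planned. Alternatively, keep the two-row model but remove the arm main effect, so that the arms share one baseline mean, as randomisation justifies, with an unstructured covariance. Either change brings the analysis into line with the stated 90/88/86%. State the formula, the two-sided alpha and the equal-SD assumption beside the power figures.

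If the interaction test is kept, restate the power as 80/78/75% (82/80/78% if baseline-only patients are included), and say which patients the complete-case set contains.

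The cost is SAP wording: same data, same patients and a model no more complex. It should be a dated amendment before unblinding. The MCQ-30 amendment of 24 March 2021 was made on that footing; the SAP does not show the blinding status after that date, so it should be confirmed first.

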**Planned statistical methods**

Test of the intervention: The effect of the intervention will be examined using the treatment group by time-point interaction term from a multi-level, mixed effects, regression model analysis combining both time-points (baseline and 4 months). The primary endpoint is HADS total score at 4 months, for which the interaction component relating to 4 months (relative to baseline) will be used.

The primary analysis will take the form of an intention-to-treat analysis using complete cases. This will be supplemented by a sensitivity analysis using multiple imputation, allowing us to assess the robustness of the results against missing values (see below). Other sensitivity analyses will be conducted as appropriate (see below). Analysis will be conducted using Stata 15 and an alpha level of 5%.

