**Planned statistical methods**

Analysis of secondary outcomes:

All of the secondary outcomes will be treated as longitudinal continuous variables. For each secondary outcome, the effect of the intervention will be examined using the 4-month trial arm by time-point interaction term from the mixed effects model. The model will have two levels: time-points within patients. Random effects will be applied to the patient-specific intercepts.

- Fixed effects: trial arm, time-point, arm x time-point, design variables (hospital site, sex), other pre-specified covariates and additional covariates (see Choice of Covariates, below).
- Random effects: patient.

Sensitivity analysis

See relevant section below

Alternative tests if violation of distributional assumptions

See distributional tests below.

1. **Sensitivity analysis**

All of the above primary and secondary analyses will be supplemented with at least one sensitivity analysis where appropriate.

Imputation methods will be used to impute missing values at both time points and the main analysis re-run using this data. Imputation will be done in two stages: first, missing baseline values will be imputed using all available variables at baseline, but excluding treatment arm; second, missing values at 4 months follow-up will be imputed, using the full set of variables and including the interaction term between treatment arm and time-point (for consistency with the analysis model). If missing data at baseline is under 5% these will be imputed with simple regression imputation, otherwise multiple imputation. Follow-up values will utilise multiple imputation.

The extent of the missing data will determine how many MI datasets will be generated.

Additional sensitivity analyses will be conducted where the outcome variable does not match the distributional assumptions of the model, and/or if trial-arm imbalance on multiple covariates is present.

1. **Distributional tests**

The distribution of each outcome variable will be examined. If for any of these, their measure of skewness or kurtosis exceeds 1 we will consider them non-normal and p-values will be validated using a bootstrap method (see Bootstrapping, below).

1. **Bootstrapping**

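### The complete-case primary analysis can drop patients whom the planned mixed model could keep, and the planned multiple imputation does not test loss that is not at random, while the two arms differed in missing 4-month HADS at the last count

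*SAP*

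**What the plan says.** For the primary outcome, the SAP (Planned statistical methods) says: "The primary analysis will take the form of an intention-to-treat analysis using complete cases". It goes on: "This will be supplemented by a sensitivity analysis using multiple imputation, allowing us to assess the robustness of the results against missing values".

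Under Analysis method, the model has two levels (time-points within patients) with a patient random intercept. HADS at baseline and at 4 months are both outcomes, and the treatment effect is the arm-by-time interaction.

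The Sensitivity analysis section describes the imputation. At the second stage, "missing values at 4 months follow-up will be imputed, using the full set of variables and including the interaction term between treatment arm and time-point", and "Follow-up values will utilise multiple imputation". No delta shift, reference-based method or tipping point is named. The section's further analyses have two triggers. The first is distributional: "Additional sensitivity analyses will be conducted where the outcome variable does not match the distributional assumptions of the model". The second is imbalance between arms on several covariates.

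Under Sample size, the table dated 06/04/2020 gives 119 (MCT+CR) and 121 (CR) patients at baseline. A 4-month HADS was available for 84 and 105 of them. The same section says that effort would go into collecting the remaining follow-ups, partly to make the arms more even.

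**The concern.** There are two separate weaknesses.

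**Complete cases.** If both time-points are required, the arm-by-time term becomes a difference in mean change among completers. It is biased when loss depends on baseline HADS and the share lost differs by arm. This happens even if the data are missing at random given baseline. The restriction also fits poorly with the intention-to-treat label, because on the 06/04/2020 counts it would leave out 51 of 240 patients.

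**No check for loss that is not at random.** Imputing from observed variables treats a patient who did not return the HADS like a comparable patient in the same arm who did. If non-returners in the self-help arm did worse than that, the completers' analysis and the imputed analysis err in the same direction. Their agreement would then say little about this form of loss, although the SAP presents imputation as the test of robustness to missing values.

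**Working it through.** **Inputs (SAP, Sample size).** Baseline 119 and 121; 4-month HADS 84 and 105; target effect 0.4 SD; baseline to follow-up correlation r = 0.5. Alpha is 5% (Planned statistical methods), taken here as two-sided. The SAP gives no HADS standard deviation, so results are in SD units.

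**1. The plan's power figures.** The residual SD after baseline adjustment is sqrt(1 - 0.5²) = 0.866. With 84 and 105, SE = 0.866 x sqrt(1/84 + 1/105) = 0.127, which gives 88.4% power (stated: 88%). With 76 and 100, power is 85.9% (stated: 86%). Both reproduce.

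**2. Missing 4-month HADS on 06/04/2020.**
- MCT+CR: 1 - 84/119 = 35/119 = 29.4%.
- CR: 1 - 105/121 = 16/121 = 13.2%.
- Difference: 16.2 points (95% CI 6.0 to 26.4; Fisher p = 0.003).
- Overall: 51/240 = 21.3%, close to the planned 20%, so the total does not show the split by arm.

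**3. Completers' change when data are missing at random.** Assume that non-responders in both arms start 0.5 SD higher than responders. Completers' mean baseline then lies below the arm mean by 0.294 x 0.5 = 0.147 SD (MCT+CR) and 0.132 x 0.5 = 0.066 SD (CR), a gap of 0.081 SD. The bias in the difference in change is (1 - r) x gap = 0.5 x 0.081 = 0.04 SD. The lower-starting MCT+CR completers regress down less, so MCT benefit is understated. The sign reverses if non-responders start lower.

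**4. Loss that is not at random.** Let delta be the amount, in SD, by which non-responders are worse than observed data predict. Overstatement of benefit is 0.294 x delta if this holds in MCT+CR only, and (0.294 - 0.132) x delta = 0.162 x delta if it holds equally in both arms.

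| delta (assumed) | MCT+CR only | Both arms |
| --- | --- | --- |
| 0.3 SD | 0.09 SD | 0.05 SD |
| 0.5 SD | 0.15 SD | 0.08 SD |
| 1.0 SD | 0.29 SD | 0.16 SD |

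**5. Tipping point, for illustration.** Take an observed effect of exactly 0.4 SD and hold the SE at 0.127, so the significance limit is 1.96 x 0.127 = 0.248. Significance is lost at delta = (0.4 - 0.248)/0.294 = 0.52 SD (MCT+CR only) or (0.4 - 0.248)/0.162 = 0.94 SD (both arms). The effect reaches zero at 0.4/0.294 = 1.36 or 0.4/0.162 = 2.47 SD. This SE assumes baseline adjustment. For a change score with r = 0.5 the SD is 1.0, the SE 0.146 and the limit 0.287, and significance would be lost at about 0.38 or 0.70 SD.

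**6. Effect of later returns.** If MCT+CR missing fell to 24/119 = 20.2% with CR unchanged, the gap would be 6.9 points. The multipliers in step 4 would fall to 0.202 and 0.069.

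**The case against.** **The counts are a snapshot.** They were taken while collection continued, and the SAP does not say how many of the 35 and 16 were lost, late or not yet due. A reader might infer that follow-up loss in the self-help arm is simply double that of control. The document does not support this: it saw the gap and set out to narrow it. The objection stands as a limit on size. It does not remove the point. Allocation was 1:1 in small blocks, so follow-ups not yet due should be similar in number by arm, and timing alone does not readily explain an excess of 35 - 16 = 19. The version amended on 24/03/2021 gives no later count.

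**The complete-case term is undefined.** It could mean only that nothing is imputed, in which case a likelihood fit would already retain patients with baseline only. This is possible. If so, the first part of the fix is a correction of wording.

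**Imputation already deals with loss that depends on baseline HADS.** This is right. A reader might infer that the plan has no protection against uneven loss, which goes too far. What remains untested is the not-at-random part. That the imputation assumes missing at random is inferred from its specification; the SAP does not use the term.

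**The deltas are not in the documents.** Also right. A one-arm deficit of 0.5 SD would shift the result by 0.147/0.4 = 37% of the target effect, and a reader might take that as an estimate of bias. It is only a scenario. The shifts in steps 3 and 4 also run in opposite directions as set out, so they must not be added up as one threat.

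**Other sensitivity analyses are allowed as appropriate.** The SAP refers the reader to its later section for these. The triggers there are distributional misfit and covariate imbalance, so nothing is committed on missing data.

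**Conclusion.** The point holds in two parts. First, the complete-case primary analysis, taken literally, drops usable patients and admits a bias that the planned model could avoid. That bias is small: about 0.04 SD in the example, with a sign that depends on who is lost. Second, no planned analysis shows how far the result depends on loss that is not at random. On the 06/04/2020 counts the overstatement is 0.09 to 0.29 SD (MCT+CR only) or 0.05 to 0.16 SD (both arms) for delta of 0.3 to 1.0 SD, and it shrinks as outstanding questionnaires return.

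These sizes rest on the snapshot counts, the plan's r of 0.5, and assumed values of delta and of the baseline difference. They show sensitivity and are not evidence that bias occurred. The stated power figures are not in error. The protocol and the last part of the SAP could not be consulted; a not-at-random analysis specified there would answer the second part.

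**What to change.** 1. In the primary analysis, replace the complete-case restriction with all randomised patients who have any HADS value, analysed in the mixed model already planned and fitted by likelihood. Keep the complete-case analysis as secondary. If this was the intention all along, say so and define the term.
2. Extend the planned multiple imputation with a pre-specified delta adjustment of imputed 4-month HADS, by arm: MCT+CR only, then both arms. Fix the range of delta in advance, and report the tipping point using the final missing counts by arm.

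The cost is a few sentences in the SAP and a short extension of an analysis already planned. The downside is a sensitivity range that may look less favourable. The 24/03/2021 amendment records that it was made before unblinding, so both changes could still have been pre-specified at that date.
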